**Randomization**

Participants meeting the inclusion and exclusion criteria will be approached, screened, consented, and enrolled into the study. After obtaining informed consent, participants will be randomized to either the experimental (RGT) or UC control group using cluster randomization based on specific injury characteristic for stratified block.

The heterogeneity of the population in terms of injury severity is a concern given that these factors are expected to be important to walking recovery. To account for this, patients will be assigned to RGT or UC using 1:1 stratified blocks. Stratification will be based on specific injury characteristics (incomplete tetraplegia and incomplete paraplegia), and within each strata randomization blocks of size 6 will be used to ensure equal distribution between groups.

[figure not shown]

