# **9 STATISTICAL METHODS**

**Sample Size Considerations**

For the proposed project, 128 patients (64 per group) will be enrolled. All analysis will be performed using SAS 9.4 significance set at the 5% level. Sample size calculations were performed to determine the required sample size in each group based on detectable effect size. For 80% power with a 5% significance level we will need to obtain 64 participants in each group to detect a medium effect size of 0.5 and allow for ~10% attrition due to unplanned medical events, acute care transfers, and patient withdrawals. We anticipate minimal attrition as all treatments and outcomes will be assessed during the inpatient rehabilitation stay and we experienced 0% attrition during our feasibility study.

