**Study Analysis Methods**

**Aim 1 Analysis.** Our Aim 1 hypothesis is:

Hypothesis 1.1: *We will successfully engage key stakeholders in a community-based participatory research approach to develop the content and structure of the RGT program to accommodate current clinical practice guidelines and integrate emerging robotic exoskeleton technology.*

The Advisory Board of key stakeholders (patients, caregivers, clinicians, researchers, industry members) to review evidence-based literature, advise the research team on the unique aspects and goals of inpatient rehabilitation for people with SCI, review the RGT, and make recommendations for amendments to the RGT program based on our interim and final outcomes of the study over the funding period. The role of the advisory board is necessary to meet the needs of individuals post SCI based on previously demonstrated successful inclusion of RGT into clinical practice during inpatient rehabilitation and detected change in key outcome variables.

**Aim 2 Analysis.** Our Aim 2 hypotheses were:

*Hypothesis 2.1:* *Patients with incomplete SCI who receive RGT will have higher walking function (WISCI-II) at discharge compared to UC.*

*Hypothesis 2.2: Patients with incomplete SCI who receive RGT will have greater improvement of secondary outcomes (gait speed, daily function independence, pain, fatigue, spasm frequency, depressive symptoms, and quality of life) at discharge compared to UC.*

All analysis will be performed using SAS 9.4 with a significance level of 0.05. To determine if patients with incomplete SCI who receive RGT will have higher walking function than UC at discharge (Hypothesis 2.1), WISCI-II scores will be evaluated using a linear model. The distribution of WISCI-II scores will be assessed to determine if a general linear model will be utilized, or if a generalized linear model with an alternative distribution and link function, such as the gamma distribution with a log link, will be more appropriate. Similarly, all measures associated with the secondary outcomes in Hypothesis 2.2 (10MWT, SCIM, NPRS, FSS, PSFS, PHQ-9, LiSAT-9) will be evaluated with general or generalized linear models, as appropriate. A separate model will be run for each outcome. All models for both the primary and secondary outcomes will control for scores at admission as well as the patient’s demographic and impairment information listed in section B.1.i.D.

**Aim 3 Analysis:** Our Aim 3 hypotheses were:

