Hypothesis 3.1: *RGT will be of significantly greater intensity with participants (1) spending more minutes per session and total minutes (over all sessions) in moderate intensity exercise (40% to 60% range of heart rate reserve), (2) reporting higher mean RPE across all sessions, and (3) completing more steps during each session and total number of steps over all sessions compared to UC.*

Hypothesis 3.2: *Intensity will be significantly correlated to the primary outcome (WISCI-II) for the RGT and UC groups.*

Hypothesis 3.1 will be evaluated using similar methods as Aim 2. Moderate intensity minutes, average RPE, and steps will be evaluated using individual general or generalized linear models, as appropriate, to determine the association between RGT and UC and intensity. Each model will control for the patient characteristics listed in section B.1.i.D and total number of sessions. Additionally, to determine the relationship between session intensity and walking function (Hypothesis 3.2) correlation coefficients will be calculated between each intensity measure and WISCI-II at admission, discharge, and change score.

For both Aims 2 and 3 stratified subset analysis will be performed for tetraplegia and paraplegia to determine if RGT has a differing impact depending on injury classification.

**Missing Data:** If a patient misses an assessment, their data for that outcome will be treated as missing and *will not* be included in the statistical model. However, the data from the completed assessments for that patient *will* be included. Sensitivity analysis will be performed to assess the impact of missing data, by imputing a missing outcome measure using the overall average change score for the given outcome. The sensitivity analyses will be compared to the initial analysis to determine the impact of missingness on the results

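### Separate tetraplegia and paraplegia analyses cannot show whether RGT works differently by injury class; an interaction estimate is needed

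*Protocol*

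**What the plan says.** Protocol section 9, Study Analysis Methods, closes the Aim 3 text with a sentence that covers both efficacy and intensity outcomes: "stratified subset analysis will be performed for tetraplegia and paraplegia to determine if RGT has a differing impact depending on injury classification". It states a purpose (to find out whether the effect differs by class) and a method (analysis by subset). It does not say how the two subset results will be compared or what would count as a difference.

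The two classes are the randomisation strata. Section 5, Randomization: "Stratification will be based on specific injury characteristics (incomplete tetraplegia and incomplete paraplegia"), with 1:1 allocation in blocks of 6. The expected split between classes is not given.

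On the models, section 9 says "All models for both the primary and secondary outcomes will control for scores at admission". The other covariates are referred to a section labelled B.1.i.D, which is not in this document. No arm-by-class term is mentioned. On the threshold: "All analysis will be performed using SAS 9.4 with a significance level of 0.05". The trial is sized for the overall comparison only: "For 80% power with a 5% significance level we will need to obtain 64 participants in each group". The standardised effect assumed there is 0.5.

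**The concern.** Whether RGT has a different effect in tetraplegia and paraplegia is a question about the difference between two treatment effects. A within-class analysis answers another question: whether RGT beats usual care in that class. Running it twice gives two answers to that second question and none to the first.

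The danger is a familiar one. One class reaches p < 0.05 and the other does not, and the trial is read as showing that RGT helps one injury class only. With about half the patients in each subset, such a split can easily arise by chance when the effect is the same in both. The trial is meant to inform clinical training programmes, so a false class-specific message would matter.

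**Working it through.** **Inputs from the protocol.** Two-arm comparison; significance level 0.05, taken as two-sided because that reproduces the sample size; standardised effect d = 0.5; 64 per arm ("128 patients (64 per group) will be enrolled"); attrition of about 10% ("allow for ~10% attrition due to unplanned medical events, acute care transfers, and patient withdrawals"), which leaves about 58 per arm.

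**Assumptions, because the protocol gives no figure.** Class split 50:50, with a range to 80:20. Correlation r between admission score and outcome from 0 to 0.8. Decision rule: significant in exactly one class counts as a difference.

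**Step 1: the plan's own figure.** The normal-approximation formula gives 63 per arm. Exact (noncentral t) power at 64 per arm and d = 0.5 is 80.1%. The stated 64 per group is therefore the two-sided t-test sample size.

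**Step 2: power in each subset.** At 50:50 there are 64/2 = 32 per arm per class. The noncentrality is 0.5/√(2/32) = 2.0, and exact power is 50.4%.

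**Step 3: chance of a discordant pair when the effects are identical.** With subset powers p1 and p2,

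P(exactly one significant) = p1(1 − p2) + p2(1 − p1).

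At 50:50 and d = 0.5 this is 2 × 0.504 × 0.496 = 50.0%. A simulation of 40,000 trials also gave 50.0%. Both subsets are significant in 0.504² = 25.4%.

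| Split (d = 0.5) | 64 per arm | 58 per arm |
|---|---|---|
| 50:50 | 50.0% | 49.8% |
| 60:40 | 51.2% | 51.0% |
| 70:30 | 55.3% | 54.5% |
| 80:20 | 61.0% | 59.1% |

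**Step 4: dependence on the common effect** (50:50, 64 per arm).

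| Common d | Power per subset | Exactly one significant |
|---|---|---|
| 0 | 5.0% | 9.5% |
| 0.2 | 12.4% | 21.7% |
| 0.3 | 21.9% | 34.2% |
| 0.5 | 50.4% | 50.0% |
| 0.8 | 88.3% | 20.7% |
| 1.0 | 97.6% | 4.7% |

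At an equal split 50% is the ceiling, because 2p(1 − p) peaks at p = 0.5. With uneven classes the rate falls more slowly at large effects: at 80:20 it is still 50.1% at d = 0.8.

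**Step 5: dependence on baseline adjustment.** If 0.5 is on the unadjusted SD, adjusting for admission score raises the effective d to 0.5/√(1 − r²). At 50:50:

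| r | Effective d | Power per subset | Exactly one significant |
|---|---|---|---|
| 0.5 | 0.577 | 62.3% | 47.0% |
| 0.7 | 0.700 | 78.7% | 33.5% |
| 0.8 | 0.833 | 90.7% | 16.9% |

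**Step 6: the direct test.** A single interaction test at two-sided 0.05, with 32 per arm per class, rejected in 4.8% of simulated trials at a common d = 0.5 and in 5.1% at d = 0. Its standard error is √(4/32) = 0.354 SD. For a true between-class difference of 0.5 SD, 0.5/0.354 = 1.41, which gives power of about 29%. For 1.0 SD it is about 81%.

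**The case against.** **No rule is stated.** The protocol does not say that significance in one class and not in the other will be read as a difference. The subset estimates and intervals could be compared instead. This stands, so the percentages above are conditional on the reading. It does not rescue the method: the sentence sets out to determine something and names no comparison that would do so.

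**The analysis plan may add an interaction.** It may. But the protocol is not silent here. It assigns the question to subset analyses, and that assignment is what needs changing.

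**The rate is not always one half.** A reader might infer that identical effects give a false difference about half the time in general. The protocol's figures do not support that. One half belongs to a common effect near 0.5 with little gain from baseline adjustment; elsewhere the rate can be far lower. The 0.5 is also a generic medium effect, and nothing ties it to the intensity measures of Aim 3.

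**The randomisation stratum.** A reader might also infer that injury class has been left out of the models. That cannot be told. The covariate list is referred to a section that is not in this document and may include it. The baseline data listed in section 6 include injury severity but do not name injury class, and that list is not identified as the covariate list.

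**Importance.** None of hypotheses 2.1, 2.2, 3.1 or 3.2 concerns injury class, and the primary WISCI-II comparison is untouched. That stands and limits the weight of the point.

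**Conclusion.** The point holds: the protocol gives a between-class question to analyses that never compare the classes. If the result is judged by subset significance, the chance of an apparent difference under identical effects is about 50% at the design effect of 0.5 and an equal split, and up to about 61% at 80:20. At an equal split it is about 10% to 34% for common effects of 0 to 0.3, and about 21% at 0.8. At 0.5 it falls to 47%, 34% or 17% for baseline correlations of 0.5, 0.7 or 0.8. An interaction test holds about 5% throughout.

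These figures rest on an assumed split, an assumed correlation and a decision rule that the protocol does not state. That the method does not fit its purpose rests on none of them. This should be corrected before analysis, but it concerns a supplementary analysis and does not threaten the primary result.

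**What to change.** For the Aim 2 models and the Hypothesis 3.1 models, replace the sentence with wording such as:

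> *Effect modification by injury class (tetraplegia or paraplegia) will be estimated by an arm-by-class interaction in the full-sample model and reported with its 95% confidence interval on the scale of the fitted model: a difference in effects for a linear model, a ratio of ratios for a log link. Class-specific effects will be taken from the same model and are descriptive. This analysis is exploratory.*

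The scale has to be stated because section 9 allows a gamma model with log link, and effects that are equal on one scale need not be equal on the other. The wording does not apply to Hypothesis 3.2, which uses correlation coefficients.

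Name injury class explicitly as a covariate in these models, since it is the randomisation stratum and the present cross-reference does not let a reader check whether it is included.

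The cost is a change of wording and one or two degrees of freedom; the variable is already collected for randomisation. The interaction will be imprecise (power about 29% for a 0.5 SD difference at an equal split), so the interval should carry the message, and a non-significant result should not be read as showing equal effects.

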# **6 STUDY MEASUREMENTS**

**Study Endpoints**

The following data will be collected through the medical record and patient interview at baseline assessment: age; age at injury; injury severity; gender; ethnicity; education level; pre-morbid history of mental illness; residence status; income; insurance type; vocation; and financial status. Level of impairment will be captured using the ASIA Impairment Scale (AIS) to determine injury severity after traumatic SCI by the physician at admission to BSW. The AIS is standard of care at BSW and will be extracted from the medical record. The following data will be collected through medical record and patient interview within one week of admission and discharge: *Gait speed via 10-Meter Walk Test, Spinal Cord Independence Measure (SCIM), Numerical Pain Rating Scale (NPRS), *Fatigue Severity Scale (FSS), Penn Spasm Frequency Scale (PSFS), Patient Health Questionnaire - 9 (PHQ-9), Life Satisfaction Questionnaire (LiSAT-9), Heart Rate (HR), Ratings of Perceived Exertion (RPE), and Number of Steps*. Primary and secondary outcomes for Aim 2 and dose parameters for Aim 3 are described in **Table 7.**

| **Table 7. Outcome Measures for Proposed Project and link to ICF** | | |
| --- | --- | --- |
| **Aim 2 Primary Outcome:** To examine the efficacy of RGT compared to usual care gait training (UC) | | |
| ****Walking Index for Spinal Cord Injury – II (WISCI-II)*** | Our primary outcome, the WISCI-II defines the physical limitation for gait secondary to impairment at the person level and indicates the ability of a person to walk after SCI.^103^ Intrarater and interrater reliability are excellent at 1.0 and 0.98 respectively.^104^ A change of one WISCI level can be considered clinically significant.^105^ | ICF domain = Activity |
| **Aim 2 Secondary Outcomes** | | |

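### As written, a patient with a measured discharge score but no admission score drops out of that outcome's model, and nothing in the plan fills the gap

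*Protocol*

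**What the plan says.** Section 5 (Visit Windows, Table 6) sets two assessments, one within a week of admission and one within a week of discharge. In Section 9, the Missing Data paragraph states: "If a patient misses an assessment, their data for that outcome will be treated as missing", and keeps those data out of the statistical model. It adds that what the patient did complete will be used. It names one imputation, a sensitivity analysis that fills a missing outcome measure with the overall average change.

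The Aim 2 analysis in the same section states: "All models for both the primary and secondary outcomes will control for scores at admission". It adds demographic and impairment information by reference to a section B.1.i.D, which is not in this document.

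Table 6 takes WISCI-II, the 10-meter walk test, SCIM and the pain scale from the medical record. The fatigue, spasm, depression, anxiety and quality-of-life scales are study-specific. Section 5 (Informed Consent) lets patients consent up to the end of day 10, and later if they were not medically suitable at first.

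**The concern.** A missed admission assessment and a missed discharge assessment are different problems, and the rule treats them alike. If the discharge score is missing, the outcome is unknown. If only the admission score is missing, the outcome is known and the gap is in a covariate. Leaving the patient out then discards a measured outcome and removes a randomised patient from the comparison, although the gap can be filled without touching the randomised contrast.

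The stake is mainly precision. It is also the principle that the randomised patients with an outcome are the ones analysed. The window problem makes this a practical risk: a study-specific scale cannot be given before consent, and permitted consent on day 10 falls after the one-week admission window has closed. The protocol does not say whether a late admission value counts as missed.

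**Working it through.** **Reading the rules together.** Take a patient with a discharge score and no admission score for one outcome.

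1. Exclusion rule: an assessment was missed, so the data for that outcome are kept out of the model.
2. Completed-assessments sentence: the discharge score should be used.
3. Model: it requires the admission score, which is blank, so a linear or generalized linear model cannot use the record unless the blank is filled.
4. Imputation: the one named method fills an outcome measure, and only in a sensitivity analysis. Used backwards on a missing admission score, it would build the baseline from the post-randomisation outcome. The protocol does not say it would be used that way.

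Step 2 therefore either refers to the patient's other outcomes or conflicts with step 3. Under either reading the patient is absent from that outcome's primary analysis.

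**The plan's own figure.** Sample Size Considerations gives: "For 80% power with a 5% significance level we will need to obtain 64 participants in each group". The standardised difference assumed there is 0.5. I assumed a two-sided test. With n per arm, the noncentrality is d × √(n/2) = 0.5 × √32 = 2.83 on 126 degrees of freedom, and the power is 80.1%. So 64 per arm is the number needed with no losses at all. (Keeping 64 after 10% attrition would need 64/0.9 = 71.1, that is 72 per arm. That is a separate point.)

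**Effect of deletion.** Inputs not in the documents, and so assumed: a share m of admission scores missing (5%, 10%, 20%), admission-discharge correlation r (0.3, 0.5, 0.7), and the 0.5 effect measured in unadjusted standard deviations. Adjustment for the admission score raises the effective effect size to 0.5/√(1 − r²), and deletion leaves 64 × (1 − m) per arm.

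Example, r = 0.3 and m = 20%: 0.5/√0.91 = 0.524; 64 × 0.8 = 51.2 per arm; power 74.7%, against 83.7% with nothing missing. With r = 0.5, the same loss gives 0.5/√0.75 = 0.577 and power 82.5%, against 90.0%.

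**Deletion against filling.** I simulated 10,000 trials per row (128 patients, 1:1, linear model with arm and admission score; simulation error about 0.4 points). Filling uses the mean over both arms plus a missing indicator.

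| r | Missing | Power, deleted | Power, filled | Gain (points) |
|---|---|---|---|---|
| 0.3 | 5% | 81.4% | 82.8% | 1.4 |
| 0.3 | 10% | 78.5% | 82.2% | 3.7 |
| 0.3 | 20% | 73.9% | 82.0% | 8.1 |
| 0.5 | 5% | 88.5% | 89.3% | 0.8 |
| 0.5 | 10% | 86.8% | 88.5% | 1.7 |
| 0.5 | 20% | 82.2% | 87.8% | 5.6 |
| 0.7 | 5% | 96.5% | 96.8% | 0.3 |
| 0.7 | 10% | 95.8% | 96.0% | 0.2 |
| 0.7 | 20% | 93.5% | 94.4% | 0.9 |

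The filled estimate averaged 0.497 to 0.501 for a true 0.5. With no true effect and r = 0.5, filling rejected in 4.7% to 5.2% of trials. With 20% missing, all of it among patients below the average admission score, it rejected in 4.9%.

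**The case against.** The strongest reply is that the protocol promises to use completed assessments, that a discharge score is one, and that the handling of missing covariates usually belongs to the SAP, which is not shown. Silence on covariates would indeed be no finding. Here, however, the protocol states an exclusion rule that reaches the admission assessment and a model that needs the admission score. The promise cannot be kept in that model as written.

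A second reply stands in large part. WISCI-II comes from the medical record at both time points, so few admission values may be missing for the primary outcome. The missing rates and correlations above are assumptions.

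A reader might go further and infer that one unanswered demographic item, such as those in "residence status; income; insurance type; vocation; and financial status", also removes a patient. The document does not say so. The exclusion rule concerns assessments, the covariate list sits in an absent section, and the inference rests on how software handles blanks by default.

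Filling also has limits. It is safe when the value was measured, or due, before randomisation, and the protocol does not fix that order for the study-specific scales. The simulation covers the linear model, not the gamma model with log link that the protocol also allows.

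**Conclusion.** The point holds for the admission score. Section 9 drops a randomised patient with a measured discharge score from an outcome's model when the admission score is missing, and the document offers no remedy in the primary analysis. The exposure is clearest for the study-specific secondary scales and may be small for WISCI-II.

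The size cannot be known from the document. Under the assumed 5% to 20% missing, the recoverable power is about 1 to 8 points at correlations of 0.3 to 0.5 and under 1 point at 0.7. A reader might conclude that power must fall below the planned 80%. That does not follow: adjustment for the admission score can more than offset the loss, as at r = 0.5 with 20% missing (82.2%). It can fall below, as at r = 0.3 with 10% missing (78.5%). This is a defect in a stated rule that is cheap to repair, and it does not by itself undermine the primary comparison.

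**What to change.** In the Missing Data paragraph of Section 9, limit the do-not-include rule to a missing discharge score and add wording such as: *A missing admission score, or any other missing baseline covariate in the model, is filled with the mean over both arms together with a missing indicator (a missing category for categorical items), without use of treatment arm or outcome. Every randomised patient with a discharge score is included in the model for that outcome.*

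State that this applies to values measured, or due, before randomisation, and say whether an admission value taken after the one-week window counts as missing. Reword the completed-assessments sentence to match.

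The cost is one or two sentences in the protocol or SAP and a little extra analysis work. No new data are needed.

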# **3 STUDY AIMS**

**Aim 1:** Use a Community-Based Participatory Research approach to develop an RGT program that meets the unique needs of people after incomplete SCI during inpatient rehabilitation. This will be achieved by establishing and engaging an Advisory Board of key stakeholders (patients, caregivers, clinicians, researchers, industry members) to review evidence-based literature, advise the research team on the unique aspects and goals of inpatient rehabilitation for people with SCI, review the RGT, and make recommendations for amendments to the RGT program based on our interim and final outcomes of the study over the funding period.

Hypothesis 1.1: *We will successfully engage key stakeholders in a community-based participatory research approach to develop the content and structure of the RGT program to accommodate current clinical practice guidelines and integrate emerging robotic exoskeleton technology.* Our hypothesis is based on the fact we have previously demonstrated the successful inclusion of RGT into clinical practice during inpatient rehabilitation and detected change in key outcome variables.

**Aim 2**: Prospectively examine the efficacy of RGT compared to usual care gait training (UC) during inpatient rehabilitation in people with incomplete SCI.

Hypothesis 2.1: *Patients with incomplete SCI who receive RGT will have higher walking function [Walking Index for Spinal Cord Injury – Revised (WISCI-II)] at discharge compared to UC.* Our hypothesis is based on our previous work showing SCI patients who received 5+ RGT sessions demonstrated greater improvement on the WISCI-II compared to UC.^10,11^

Hypothesis 2.2*: Patients with incomplete SCI who receive RGT will have greater improvement in secondary outcomes (gait speed, daily functional independence, pain, fatigue, spasm frequency, depressive symptoms, and quality of life) at discharge compared to UC.*

**Aim 3**: Compare the intensity of RGT and UC gait training during inpatient rehabilitation. Intensity data will include (1) heart rate, (2) rate of perceived exertion (RPE), and (3) number of steps.

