**Visit Windows**

Patients will be asked to complete testing at 2 time points: within one week of admission to inpatient rehabilitation and within one week of discharge from inpatient rehabilitation.

| **Table 6: Patient Timeline** | | | | |
| --- | --- | --- | --- | --- |
| Study Phase | Admission | Treatment (UC or RGT) Intervention | Discharge | Data Source |
| **Consent** | X |  |  |  |
| Demographics | X |  | X | Medical Record |
| **Outcome Testing** |  |  |  |  |
| *Aim 2* |  |  |  |  |
| Walking Score Index for Spinal Cord Injury (WISCI-II) | X |  | X | Medical Record |
| 10-meter walk test (10MWT) | X |  | X | Medical Record |
| Spinal Cord Independence Measure (SCIM) | X |  | X | Medical Record |
| Numeric Pain Rating Scale (NPRS) | X |  | X | Medical Record |
| Fatigue Severity Scale (FSS) | X |  | X | Study Specific |
| Penn Spasm Frequency Scale (PSFS) | X |  | X | Study Specific |
| Patient Health Questionnaire – 9 (PHQ-9) | X |  | X | Study Specific |
| General Anxiety Disorder – 7 (GAD – 7)  International SCI Quality of Life Basic Data Set  Qualitative Questionnaire | X  X |  | X  X  X | Study Specific  Study Specific  Study Specific |
| *Aim 3* |  |  |  |  |
| Heart Rate (HR) |  | X |  | Study Specific |
| Ratings of Perceived Exertion (RPE) |  | X |  | Study Specific |
| Number of steps |  | X |  | Study Specific |

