**Risks and Benefits**

*Physical risks***:** Participants may experience orthostatic hypotension, skin breakdown, falls, fracture, overheating, and autonomic dysreflexia if they have difficulty due to impaired motor and sensory function common to SCI population. All therapy staff is trained to observe and monitor for these risks and methods to limit or resolve these potential concerns.

*Psychological risks***:** Participants may experience frustration during RGT due to motor and sensory deficits common to SCI population. All staff is trained to observe and monitor for frustration and methods to limit or resolve these potential concerns (i.e. institute rest breaks, maintain supervision).

*Social risks***:** No social risks have been identified by participating in this study.

*Legal risks***:** No legal risks have been identified by participating in this study.

*Economic risks*: No economic risks have been identified by participating in this study.

*Direct benefit to research participants*

See below for potential future benefits.

*Potential future benefits to individuals with the condition being studied*

The benefits to participants may include gaining greater walking function and improved health. Study findings could help rehabilitation clinicians identify evidence-based practice walking interventions and facilitate best practice guidelines for patients with SCI.

*Potential benefits to society in general*

The information gained in this study will help validate the importance and benefits of exoskeleton gait training in the outpatient rehabilitation setting for spinal cord injury patients.

*Potential benefits to others involved in research*

Clinicians involved in this research will contribute to evidence-based practice research methods, and facilitation of improvements for best practice for spinal cord injury patients.

*Risk to benefit analysis*

The risks posed to study subjects (e.g. injury while engaging in physical activity, psychological stress associated with treatment) are minimal, while the study poses benefits to the study participants in terms of improved walking recovery after SCI and overall health and function. The research poses potentially great benefits to society, as individuals with SCI and rehabilitation clinicians desire enhanced walking recovery to allow greater independence with mobility for activities and community participation.

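### The primary WISCI-II model leaves out every randomised patient without a discharge score, although the expected losses are partly health-related and the one sensitivity analysis cannot test whether those patients did worse

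*Protocol*

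**What the plan says.** Aim 2 is to "Prospectively examine the efficacy of RGT compared to usual care gait training (UC) during inpatient rehabilitation in people with incomplete SCI". Hypothesis 2.1 makes WISCI-II at discharge the primary comparison. The Aim 2 analysis fits a general or generalised linear model that controls for the admission score and for demographic and impairment information.

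Testing takes place twice, "within one week of admission to inpatient rehabilitation and within one week of discharge from inpatient rehabilitation" (Visit Windows). Table 6 gives the medical record as the source of WISCI-II.

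For a patient who misses an assessment, the Missing Data paragraph says "their data for that outcome will be treated as missing and *will not* be included in the statistical model". It adds: "However, the data from the completed assessments for that patient *will* be included". One sensitivity analysis is planned, "by imputing a missing outcome measure using the overall average change score for the given outcome", to be compared with the main result.

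Sample Size Considerations says that the enrolment figure will "allow for ~10% attrition due to unplanned medical events, acute care transfers, and patient withdrawals". It then continues: "We anticipate minimal attrition as all treatments and outcomes will be assessed during the inpatient rehabilitation stay", and reports 0% attrition in the feasibility study.

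**The concern.** With only two test times and a model for the discharge score, a randomised patient who has an admission score but no discharge score contributes nothing to the primary comparison. Keeping that patient's completed assessments rescues only other outcomes.

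Two of the three named causes of loss, medical events and acute-care transfers, are matters of health and plausibly related to walking recovery. If such losses are more frequent in one arm, the poorer results leave that arm's mean more often, and the comparison of completers is no longer the comparison of the groups as randomised. The admission score and covariates remove this only so far as they explain both the loss and the outcome.

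The sensitivity analysis should show whether this matters. Instead it gives every lost patient the same average improvement, whatever the arm or reason for exit.

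**Working it through.** **1. The plan's own figure.** Inputs from Sample Size Considerations: 80% power, 5% level (two-sided assumed), effect 0.5 SD. A two-sample t-test needs 63.8, so 64 per group, which matches the stated 64 with nobody lost. With 10% lost under the complete-case rule, 64 × 0.90 = 57.6 per arm remain and power is 75.8%. That the 64 holds no attrition allowance is a separate point; it is shown here because the exclusion rule turns expected attrition directly into lost patients. Overall, 10% of 128 is about 13 patients.

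**2. Size of the bias in closed form.** Let p_R and p_U be the loss shares, and let lost patients score g SD below completers of their own arm after adjustment. Then

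bias (completers minus all randomised) = g × (p_R − p_U).

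The protocol gives neither g nor loss by arm, so the splits and g = 0.5 to 1.0 are assumptions.

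| Loss RGT / UC | Bias, g = 0.5 | Bias, g = 1.0 |
|---|---|---|
| 10% / 10% | 0 | 0 |
| 15% / 5% | 0.5 × 0.10 = +0.05 SD | 1.0 × 0.10 = +0.10 SD |
| 5% / 15% | −0.05 SD | −0.10 SD |

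A positive sign favours RGT. In patients, 15% / 5% is 64 × 0.15 = 9.6 against 64 × 0.05 = 3.2.

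**3. Effect on the test, with the planned admission adjustment.** Simulated trials with no true effect, 64 per arm, probability of loss proportional to exp(−discharge score), and a linear model on arm and admission score. The admission-discharge correlation is assumed.

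| Loss RGT / UC | Correlation | Mean bias | False positives favouring RGT (nominal 2.5%) |
|---|---|---|---|
| 15% / 5% | 0.5 | about +0.084 SD | about 7.5% |
| 15% / 5% | 0.7 | about +0.06 SD | about 6.2 to 6.6% |
| 10% / 10% | 0.5 or 0.7 | about 0 | about 2.5% |

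At 5% / 15% the bias is about −0.06 to −0.09 SD. With 6,000 trials the simulation error on a rate of 7% is √(0.07 × 0.93 / 6,000) = 0.3 percentage points. Without adjustment the 15% / 5% case gives about 0.11 SD and 8.6 to 9.5%, but that is not the planned model. If loss depends on the admission score alone, the adjusted bias is about zero and the rate about 2.5%.

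**4. What the planned sensitivity analysis can show.** Take 10% loss in each arm and a completer difference of 0.50 SD. Giving all lost patients the overall average change yields 0.50 × 0.90 = 0.45 SD. The within-arm variance becomes 0.90 + 0.10 × 0.90 × 0.25² = 0.906 (SD 0.95), and the naive standard error falls from √(2/57.6) = 0.186 to √(2 × 0.906/64) = 0.168. The test statistic is 0.45/0.168 = 2.67, against 0.50/0.186 = 2.68 for completers. The estimate moves because of the value put in, not because of anything known about the lost patients, and the result would be the same had they done badly.

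**The case against.** The protocol expects minimal attrition and cites 0% in the feasibility study; with no loss there is no bias. Withdrawals are among the named causes and need not be health-related. The model adjusts for admission score and patient characteristics, which removes part of any selection. A sensitivity analysis does bring the missing patients back, so a reader who infers that RGT is judged only on patients well enough to finish goes too far: that describes the primary model, not the whole plan.

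A reader might also infer that the rule favours RGT. The documents do not support this. Risks and Benefits says "Participants may experience orthostatic hypotension, skin breakdown, falls, fracture, overheating, and autonomic dysreflexia", but ties this to motor and sensory impairment common in SCI and does not assign it to RGT; UC patients also train on the treadmill and overground. No loss by arm is given, and the bias reverses if UC loses more. Nor does any passage say that patients who leave early gain nothing from RGT.

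Finally, Table 6 promises no WISCI-II between admission and discharge, so a usable score near exit may not always exist. A final transfer might even be read as falling within the discharge window already, although Sample Size Considerations counts transfers as attrition.

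These points limit the size and remove any claim about direction. They do not change the exclusion rule or make the sensitivity analysis informative.

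**Conclusion.** The concern holds in a limited form. The primary analysis is complete-case by a written rule, the losses the plan allows for are partly health-related, and the only missing-data check assumes that lost patients improved like the average patient with data, so it cannot test the risk.

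The bias is conditional. With admission adjustment and an assumed correlation of 0.5 to 0.7, it is about 0.06 to 0.09 SD (12 to 18% of the assumed 0.5 SD effect) toward RGT at an assumed 15% / 5% loss, with about 6.5 to 7.5% false positives in that direction instead of 2.5%. It is the same size against RGT at 5% / 15%, and about zero with equal loss under no true effect, with no loss, or with loss explained by the admission score. These figures rest on loss that depends on the discharge score itself, the unfavourable case. Neither direction nor size can be established from the protocol.

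**What to change.** Replace the exclusion rule for the primary outcome:

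- Analyse all randomised patients in their allocated arm.
- For a patient who stops the intervention or withdraws but remains an inpatient, use the actual discharge WISCI-II from the medical record where consent allows. Leaving the study does not end the stay, so an earlier score should not stand in for it.
- For a transfer that finally ends the rehabilitation stay, use the WISCI-II charted within the existing one-week window before exit.
- Where no such score exists, keep the adjusted model and replace the overall-average-change imputation with arm-specific multiple imputation that assigns progressively worse outcomes to patients lost for medical reasons, varied separately in each arm. Imputing only from admission score and stratum would add almost nothing to the adjusted complete-case model.
- Keep the completers-only model as a supporting analysis, and report losses by arm and reason.

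The cost is a change of wording, some record abstraction and modest analysis work, with no added patients or procedures. Exit scores taken early in a stay may make the stated effect somewhat smaller.
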